**Process measures of navigation**

The following information will be collected to better understand the processes of navigation.

1. *Navigator demographic survey* – This instrument will be administered to all navigators to describe demographic characteristics of navigators. See NOVA Data Dictionary Table 5 for description. Please note that this information will be collected by NOVA for program evaluation and will not be available or used by project staff at the Moffitt Cancer Center.

2. *Navigator tracking log* – A log will be maintained by each navigator documenting the processes of patient navigation. The information that will be collected is documented in the NOVA Data Dictionary (Table 11). This log will document the type, length, and number of encounters navigators have with patients (Table 11a), the barriers to care that patients self-identify (Table 11b), and the actions navigators take to address patient barriers (Table 11c). In addition, data will be collected in such a way that specific navigator actions and work times can be correlated with barriers that were addressed (Table 11d).

3. *Patient navigator performance checklist* – The performance checklist will be administered by the navigator’s supervisor at least two times each year. The information to be collected in this checklist is described in Table 13 of the NOVA Data Dictionary.

4. *Clinic/Navigator Satisfaction Instruments*. - To assess constructs that relate to satisfaction with the navigator system, we will administer satisfaction instruments to clinic staff, primary care providers, and patient navigators at least yearly.

| **Navigator system related data** | **Data Source** |
| --- | --- |
| Demographics of Navigators | Navigator survey |
| Age | Navigator survey |
| Gender | Navigator survey |
| Race-ethnicity | Navigator survey |
| Primary language | Navigator survey |
| Secondary languages | Navigator survey |
| Socioeconomic status | Navigator survey |
| Educational degrees (field, degree) | Navigator survey |
| Relevant training / experience | Navigator survey |

| **Clinic / Navigator Survey** | **Data Source** |
| --- | --- |
| **Clinic staff** |  |
| Acceptance of navigator system by staff | Clinic / navigator survey |
| Acceptance of navigator system by PCP’s | Clinic / navigator survey |
| Perceived strengths of navigator system | Clinic / navigator survey |
| Perceived weaknesses of navigator system | Clinic / navigator survey |
|  |  |
| **Navigator staff** |  |
| Description of training | Clinic / navigator survey |
| Description of key resources used | Clinic / navigator survey |
| Patient load | Clinic / navigator survey |
| Time Diaries for Imputing Navigator Costs | Clinic/navigator survey |
| Perceived maximum patient load | Clinic / navigator survey |
| Job satisfaction | Clinic / navigator survey |
| Perceived strengths of navigator system | Clinic / navigator survey |
| Perceived limitations of navigator system | Clinic / navigator survey |

**D.4.6a Contamination**

Contamination is a concern to the extent that patient navigation services are provided to control sites. Contamination will reduce the apparent efficacy of patient navigation, biasing this estimate toward the null. We will take the following steps to reduce contamination. First, we will conduct site assessments and interviews with key staff to understand the current systems of patient navigation at control clinics. We will educate clinical providers and office staff at control sites about the nature of the study and the need to use existing systems of care rather than attempting to use navigator services at intervention clinics. We will remind control sites that they will receive navigation services later in the study. We will also offer control clinics basic educational materials (brochures etc.) outlining resources that are available in the community. If control patients, providers, or office staff seek out navigation services at intervention clinics they will be referred to appropriate clinical staff at their existing clinic. We will also monitor the extent of contamination of navigation services at control sites. Our community advisory board and focus groups will also make recommendations to reduce contamination.

**D.4.6b Referral Bias**

A comparison of outcomes between navigated and control subjects may be biased if providers selectively refer subjects into the study. Providers may selectively refer patients that they judge to be in most need of navigation (i.e. those subjects having the most barriers to care). This would tend to bias results toward the null. To assess whether selective referral occurs and the magnitude of its effect, we will undertake the following assessment.

First we will conduct a brief survey of providers that inquires whether providers are more likely to refer selected patients for navigation and if so what are the patient characteristics associated with greater likelihood of referral. This self administered survey will be distributed to all providers (n~35) and responses summarized. Descriptive statistics will be used to describe provider referral patterns but no hypotheses will be formally tested.

The second assessment of potential referral bias will be conducted using medical record abstraction. We will identify patients meeting eligibility criteria for navigation using administrative data sources (billing records, referral logs, tickler systems). Medical records will be abstracted to assess study outcomes and allow comparisons between eligible subjects that were referred for navigation and subjects who were eligible but not referred. We will compare these two groups in regard to the main study outcome (time to definitive diagnosis) and by patient characteristics. We hypothesize that providers will selectively refer subjects having more barriers to care). We will abstract the medical records of up to 100 subjects per intervention clinic (700 subjects total). The sample size specified will provide >80% power to detect a standardized effect size of 0.15 in comparing outcomes between referred and non-referred intervention subjects.

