###### **D.4.3 Patient Recruitment**

As described previously, seven clinics will provide the Navigator Program and five clinics will not provide the Navigator Program based on random assignment. A description of the Navigator Program to be provided at those clinics randomized to this condition follows. We will make no attempt to alter the delivery of services at those clinics not randomized to deliver the Navigator Program. Rather, we will use both observational and survey methods to characterize the processes that typically occur in these clinics once patients are identified as having a breast or colorectal abnormality. These data will be used to characterize the extent to which delivery of care differed in our two intervention conditions.

The eligibility criteria were defined in D.2.1 above. Subjects having cancer-related abnormalities will be identified by research assistants using a variety of methods. Methodologies for identifying patients will be refined and pilot tested in the project’s first year. Procedures for subject identification and recruitment will be identical for intervention and control clinics. Once identified, patients will be contacted by research assistants for recruitment into the study. Research assistants will use the following sources to identify patients:

*Appointment records*: Appointment records provide the reason for each patient’s visit and will be assessed weekly by research assistants. This information will be used to identify cancer related symptoms (i.e. breast lumps, rectal bleeding).

*Screening logs*: Participating clinics maintain screening logs to document completion of cancer screening tests such as Pap smears, mammograms, and FOBT. Research assistants will track screening logs on a weekly basis to identify patients having abnormal results on mammography or FOBT.

*Referral coordinators*: Research assistants will also make at least weekly contact with referral coordinators at each clinic to identify patients who may have been referred for cancer related problems.

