**D.4.7.b Statistical Analysis and Study Power**

The statistical analyses will focus on those subjects receiving an abnormal or suspicious mammogram (BIRAD 0, 4, or 5) and those with abnormal FOBTs or abnormalities detected on sigmoidoscopy (see D.2.1). Those in the Navigator intervention groups will be compared to those in the control groups with respect to two outcomes. For patients with breast or colorectal abnormalities, the primary outcome will be time from detection of abnormality to definitive diagnosis, measured as a continuous variable. In addition, we will assess the proportion of patients who successfully complete an appropriate diagnostic evaluation. The records of each subject with such an indication for follow-up will be examined as described in D.3.3.

Study power is based on the following factors. The primary endpoint is ‘Length of time’ (LOT=time from screening to definitive diagnosis). Suppose LOT follows a normal distribution (mean=30 days, “std” = standard deviation). Then, to detect the difference in LOT between two groups (navigator versus control groups), a two-sample t-test will be used. The required minimum sample size to achieve 80% statistical power is calculated based on the t-test and illustrated in Figure 1.

For example, group sample sizes of 29 and 29 (total 58) achieve 80% power to detect a difference of 10 days between the null hypothesis that both group means are 30.0 and the alternative hypothesis that the mean of Navigator group is 20 days with estimated group standard deviations of 15.0 each and with a significance level of 0.05 using a one-sided two-sample t-test. However, to detect a difference of 5 days with the same standard deviation 15.0 between the two groups, one would need at least 112 samples for each group (total 224).

Figure 1. Required sample sizes for each group based on the expected mean of navigator group by the standard deviation. For the control group, the mean value of LOT was set up as 30.0. The standard deviations for both groups are assumed to be equal. α=0.05 (one sided: mean 1 > mean 2).

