Although we do not expect attrition of clinics, we have assessed power the possibility of between 6 and 8 participating clinics enrolling about 100 subjects each (a total of 600 - 800 subjects). Depending on the intracluster correlation coefficient (ICC) and the design effect, however, there may be effectively fewer subjects enrolled in this study from a statistical perspective. Assuming the intracluster correlation coefficient (ICC) to be in the range of 0.01 through 0.04, the effective sample sizes will be obtained as follows,

| # of total clinics | Actual Sample Sizes | ICC | Design Effect | Effected Sample Sizes |
| --- | --- | --- | --- | --- |
| 8 | 800 | 0.01 | 1.99 | 402 |
| 6 | 600 | 0.01 | 1.99 | 302 |
| 8 | 800 | 0.02 | 2.98 | 268 |
| 6 | 600 | 0.02 | 2.98 | 201 |
| 8 | 800 | 0.04 | 4.96 | 161 |
| 6 | 600 | 0.04 | 4.96 | 121 |

Therefore, given our expected sample sizes (600-800 subjects) even under the most conservative conditions (low design effects or ICC values, and relatively high population standard deviation), we will expect the desired statistical power will be achieved.

We will also conduct a number of secondary analyses in an exploratory fashion. For those with a suspicious screening result, we will compute the Kaplan-Meier curves for time from the suspicious result to definitive diagnosis (positive or negative) for each randomized arm. For those with positive diagnoses, we will compute Kaplan-Meier curves for time to onset of therapy for each randomized arm from both suspicious screening result and definitive diagnosis. In each case, we will estimate the standard error of these estimates with Greenwood’s formula and produce 95% confidence bands for these curves using the method of Hall and Wellner. The log rank test will be used to compare the two randomized groups. These comparisons will be at the two-sided 0.05 significance level.

Degree of adherence to NCCN standards will be assessed by an independent assessor blinded with respect to randomized arm and rated as 1 = complete adherence, 2 = substantial adherence, or 3 = poor adherence. The two randomized arms will be compared with respect to these adherence ratings using Wilcoxon’s Rank Sum Test.

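### D.4.6b claims more than 80% power for a 0.15 SD referral difference from 700 charts in total; if the 700 cover both groups, power is at most about 51% (two-sided) or 63% (one-sided), and the section does not give the group sizes that would support the claim

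*Protocol*

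**What the plan says.** Protocol section D.4.6b describes two assessments of selective referral: a descriptive provider survey and a chart comparison. The chart comparison finds eligible patients from administrative sources and abstracts their records to "allow comparisons between eligible subjects that were referred for navigation and subjects who were eligible but not referred". On the analysis it says: "We will compare these two groups in regard to the main study outcome (time to definitive diagnosis) and by patient characteristics".

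The size is given as "We will abstract the medical records of up to 100 subjects per intervention clinic (700 subjects total"). The next sentence makes the power claim: "The sample size specified will provide >80% power to detect a standardized effect size of 0.15". D.4.3 confirms the clinic count: "seven clinics will provide the Navigator Program and five clinics will not provide the Navigator Program based on random assignment".

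D.4.6b does not say how the 700 divide between referred and non-referred patients, and it gives no alpha or sidedness. Elsewhere the protocol uses both conventions. The main power calculation in D.4.7.b works "with a significance level of 0.05 using a one-sided two-sample t-test", while for its Kaplan-Meier and log-rank analyses the same section says "These comparisons will be at the two-sided 0.05 significance level".

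**The concern.** The only sample size in the section is a total of 700, and the comparison has two groups. A standardized difference of 0.15 is small and needs several hundred patients per group. A total of 700 split in two looks too small for the stated power, by roughly a factor of two.

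The section itself expects selective referral and says it would pull the trial's main result toward the null. The chart comparison is meant to show whether this happens and how large it is. If its power is well below the printed figure, a non-significant difference carries less information than a reader of the protocol would assume.

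**Working it through.** **Inputs**
- Total charts: 7 clinics × 100 = 700, a ceiling (D.4.6b; clinic count from D.4.3).
- Standardized effect: d = 0.15 (D.4.6b).
- Stated power: above 80% (D.4.6b).
- Alpha: 0.05, one-sided or two-sided. This is an assumption taken from D.4.7.b, because D.4.6b gives none.
- Test: two-sample t-test with equal SDs and independent patients, as in D.4.7.b. The outcome, time to definitive diagnosis, is treated as continuous.

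**Formula**

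The noncentrality is λ = d / √(1/n₁ + 1/n₂). Power is approximately Φ(λ − z), with z = 1.960 (two-sided) or 1.645 (one-sided). The percentages below come from the noncentral t, which agrees with this approximation to about 0.1 percentage point.

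**Check of the method on the plan's own examples**

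D.4.7.b gives 29 per group for 10 days and 112 per group for 5 days, with SD 15 and one-sided 0.05. The same calculation returns 80.6% and 80.0%, so it matches the plan's method.

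**Reading 1: the 700 cover both groups**

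For 350 v 350, λ = 0.15 / √(2/350) = 1.984.
- Two-sided: Φ(1.984 − 1.960) ≈ 51%.
- One-sided: Φ(1.984 − 1.645) ≈ 63%.

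| Split of 700 | Two-sided | One-sided |
|---|---|---|
| 350 / 350 | 50.9% | 63.2% |
| 467 / 233 | 46.3% | 58.8% |
| 560 / 140 | 35.4% | 47.7% |

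An equal split is the best case, so no division of 700 reaches 80% under either convention.

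Number per group for 80% power: 2 × (z + 0.842)² / 0.15².
- Two-sided: 2 × 2.802² / 0.0225 ≈ 698 per group, about 1,396 in all.
- One-sided: 2 × 2.486² / 0.0225 ≈ 550 per group, about 1,100 in all.

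Effect detectable with 80% power at 350 v 350: (z + 0.842) × √(2/350).
- Two-sided: 2.802 × 0.0756 = 0.21 SD.
- One-sided: 2.486 × 0.0756 = 0.19 SD.

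**Reading 2: the 700 are one group only**

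| Non-referred v referred | Two-sided | One-sided |
|---|---|---|
| 700 v 350 | 62.9% | 74.1% |
| 700 v 467 | 70.8% | 80.6% |
| 700 v 500 | 72.6% | 82.0% |
| 700 v 700 | 80.1% | 87.7% |
| 700 v 933 | 85.0% | 91.2% |

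With 700 in one group, 80% power needs about 700 in the other (two-sided) or roughly 450 (one-sided, from 1 / [(0.15/2.486)² − 1/700] ≈ 452).

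The protocol does not fix the referred number, but these figures bear on it:
- D.4.7.b assumes about 100 enrolled per clinic. Over seven intervention clinics that is about 700.
- Section E allows at most 1,600 in Phase II. Seven twelfths of that is about 933, as an upper bound.
- The 600 to 800 total in D.4.7.b ("given our expected sample sizes (600-800 subjects") is for 6 to 8 clinics. It should not be split 7:5 as if it belonged to the 12-clinic design.

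**The case against.** The strongest reply is that the 700 may be only the non-referred sample. D.4.5 already provides for abstracting the charts of navigated patients, so the new abstraction in D.4.6b could be the comparison group alone. At about 100 enrolled per clinic, the seven intervention clinics would supply about 700 referred patients, and 700 v 700 gives 80.1% at two-sided 0.05. That match to the printed figure is close enough to take seriously. This part of the reply stands: the text does not rule the arrangement out, so the defect may be unclear wording and not a wrong calculation. It does not remove the point, because D.4.6b states a total, describes one abstraction that serves both groups, and never gives a referred number.

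Three stronger readings are tempting, and the documents do not support them.
- A reader might infer that a null result would be taken as proof of no referral bias. D.4.6b has no decision rule for a null result, and part of its stated aim is to gauge the size of the effect. It also compares patient characteristics and surveys providers, and D.4.3 identifies patients through appointment records and screening logs as well as referral coordinators.
- A reader might convert 0.15 SD to 2.25 days (0.15 × 15) and set it against 5 days as harm to the main result. Both the SD of 15 and the 5 days are worked examples in D.4.7.b. A gap between referred and non-referred patients is also not the bias in the comparison of arms.
- A reader might say the claim is true only with 700 in each group. At one-sided 0.05 it also holds with 700 against roughly 450 or more.

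**Conclusion.** On its plain wording the power statement in D.4.6b is wrong: 700 charts in total give at most about 51% (two-sided) or 63% (one-sided) for 0.15 SD, not more than 80%. Actual power could be lower, because 100 per clinic is a ceiling and an unequal split loses power. On the alternative reading the statement can hold, but only with a referred-group size and a sidedness that the section does not give. The same edit is needed either way.

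The conclusion assumes alpha 0.05, a two-sample t-test with equal SDs, and independent patients. It does not depend on the choice of sidedness under the plain reading, since both conventions fall short.

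The severity is moderate. This is an ancillary check on bias; it does not affect the primary analysis or the main sample size.

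**What to change.** In D.4.6b, state the number of referred and non-referred charts, the alpha and the sidedness, and make the power statement match.
- If 700 is the total, replace the power sentence with: *350 referred and 350 non-referred charts give 80% power for about 0.21 SD at two-sided 0.05 (about 51% for 0.15 SD).*
- If 700 is the non-referred group only, say so, name the source and number of the referred group, and give the resulting power.

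In either case, report the difference between referred and non-referred patients with a 95% confidence interval, so that a non-significant result is not over-interpreted.

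The cost is a sentence or two of protocol wording. No extra charts are needed. The downside is a less favourable printed figure if 700 is the total.

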**D.4.7.a** **Outcomes**

The primary outcome for this study is the time interval (in days) between abnormal finding suspicious for cancer and resolution. The onset of this time interval is the date of the abnormality meeting eligibility criteria *(Breast:* date that abnormal mammogram/US/MRI read by radiologist, date of abnormal clinical examination finding. *Colorectal:* date of abnormal screening [date sigmoidoscopy/colonoscopy performed, date FOBT interpreted], date that abnormal imaging test read by radiologist). If more than one abnormality meets eligibility criteria the onset of this time interval will begin with the earliest abnormality. Resolution is defined as the date that a definitive diagnosis is rendered regarding the initial abnormality. For breast, resolution may be indicated by definitive pathologic/cytologic findings (for women who undergo biopsy), definitive radiologic diagnosis, or by expert opinion (from breast surgeon). For colon, resolution will be defined by the date that pathologic interpretation of a biopsy specimen is rendered (if biopsy is performed) or by the date of diagnostic colonoscopy / radiologic imaging if no biopsy is performed. If more than one abnormality meets eligibility criteria resolution will be defined for the most clinically serious abnormality diagnosed (e.g. invasive cancer>>cancers in situ>>benign pathologic findings>>definitive radiological tests)

**D.4.7.b Statistical Analysis and Study Power**

The statistical analyses will focus on those subjects receiving an abnormal or suspicious mammogram (BIRAD 0, 4, or 5) and those with abnormal FOBTs or abnormalities detected on sigmoidoscopy (see D.2.1). Those in the Navigator intervention groups will be compared to those in the control groups with respect to two outcomes. For patients with breast or colorectal abnormalities, the primary outcome will be time from detection of abnormality to definitive diagnosis, measured as a continuous variable. In addition, we will assess the proportion of patients who successfully complete an appropriate diagnostic evaluation. The records of each subject with such an indication for follow-up will be examined as described in D.3.3.

Study power is based on the following factors. The primary endpoint is ‘Length of time’ (LOT=time from screening to definitive diagnosis). Suppose LOT follows a normal distribution (mean=30 days, “std” = standard deviation). Then, to detect the difference in LOT between two groups (navigator versus control groups), a two-sample t-test will be used. The required minimum sample size to achieve 80% statistical power is calculated based on the t-test and illustrated in Figure 1.

For example, group sample sizes of 29 and 29 (total 58) achieve 80% power to detect a difference of 10 days between the null hypothesis that both group means are 30.0 and the alternative hypothesis that the mean of Navigator group is 20 days with estimated group standard deviations of 15.0 each and with a significance level of 0.05 using a one-sided two-sample t-test. However, to detect a difference of 5 days with the same standard deviation 15.0 between the two groups, one would need at least 112 samples for each group (total 224).

Figure 1. Required sample sizes for each group based on the expected mean of navigator group by the standard deviation. For the control group, the mean value of LOT was set up as 30.0. The standard deviations for both groups are assumed to be equal. α=0.05 (one sided: mean 1 > mean 2).

Although we do not expect attrition of clinics, we have assessed power the possibility of between 6 and 8 participating clinics enrolling about 100 subjects each (a total of 600 - 800 subjects). Depending on the intracluster correlation coefficient (ICC) and the design effect, however, there may be effectively fewer subjects enrolled in this study from a statistical perspective. Assuming the intracluster correlation coefficient (ICC) to be in the range of 0.01 through 0.04, the effective sample sizes will be obtained as follows,

| # of total clinics | Actual Sample Sizes | ICC | Design Effect | Effected Sample Sizes |
| --- | --- | --- | --- | --- |
| 8 | 800 | 0.01 | 1.99 | 402 |
| 6 | 600 | 0.01 | 1.99 | 302 |
| 8 | 800 | 0.02 | 2.98 | 268 |
| 6 | 600 | 0.02 | 2.98 | 201 |
| 8 | 800 | 0.04 | 4.96 | 161 |
| 6 | 600 | 0.04 | 4.96 | 121 |

Therefore, given our expected sample sizes (600-800 subjects) even under the most conservative conditions (low design effects or ICC values, and relatively high population standard deviation), we will expect the desired statistical power will be achieved.

We will also conduct a number of secondary analyses in an exploratory fashion. For those with a suspicious screening result, we will compute the Kaplan-Meier curves for time from the suspicious result to definitive diagnosis (positive or negative) for each randomized arm. For those with positive diagnoses, we will compute Kaplan-Meier curves for time to onset of therapy for each randomized arm from both suspicious screening result and definitive diagnosis. In each case, we will estimate the standard error of these estimates with Greenwood’s formula and produce 95% confidence bands for these curves using the method of Hall and Wellner. The log rank test will be used to compare the two randomized groups. These comparisons will be at the two-sided 0.05 significance level.

Degree of adherence to NCCN standards will be assessed by an independent assessor blinded with respect to randomized arm and rated as 1 = complete adherence, 2 = substantial adherence, or 3 = poor adherence. The two randomized arms will be compared with respect to these adherence ratings using Wilcoxon’s Rank Sum Test.

All comparisons of the Navigator Program to the control group will be based on the ‘intent to treat principle’. That is, all patients who give consent and are registered on the study will be analyzed according to the randomized group assignment without regard to their degree of participation. Additional analyses, limited to those assigned to the Navigator Program, will explore the effects of degree of participation on the study endpoints. These analyses will incorporate participation ratings of 0 = no participation, 1 = some participation, 2 = substantial or complete participation that will be given to each patient by the Navigator assigned to that patient. Although outcome data on those patients refusing to consent in the study will not be available, we will compare those refusing to those agreeing to participate with respect to demographic variables such as age, race, gender, etc.

